### Data management

Quantitative data (summarized in Table 1) will be collected from both the intervention and control arms of the study by study researchers in the participants’ homes and by telephone. The data will comprise a range of self-report questionnaires. Response cards will be used for questions that have a range of possible responses. Home visits will be made at baseline, when participants’ infants are two and twelve months old with a telephone contact when infants are six months old. At 12 months postpartum, data collection will also include independent video-recorded observations of the mother and infant. Researchers will administer questionnaires orally where required with the anticipation that some participants may have low levels of literacy. Researchers will be trained together to ensure that similar methods are used in all locations and the trial manager will accompany them on a percentage of home visits throughout the study to maintain quality.

**Table 1 T1:** Details and timing of data collection

**Measure**	**Baseline, gestation 10 to 14 weeks**	**Infant 2 months, home visit**	**Infant 6 months, telephone interview**	**Infant 12 months, home visit**
Adult-Adolescent Parenting Inventory (AAPI-2)	X			X
CARE index				X
Demographics	X	X (update)	X (update)	X (update)
Edinburgh Postnatal Depression Scale (EPDS)	X	X	X	X
Infant feeding	X (plans)	X	X	
Infant immunizations		X		X
Maternal drug use	X	X (update)		X (update)
Maternal quality of life (EQ-5D 5L)	X	X	X	X
Maternal smoking and alcohol use	X	X (update)		X (update)
Parenting stress index short form (PSI)		X		X
Perceived parenting competence (PSOC)		X		X
Relationship violence	X			X
Social networks (MOS)	X			X
Service use		X	X	X

Data will be double entered to ensure quality and a percentage of completed forms reviewed for quality. All LSHTM data will be managed and stored in compliance with ICH GCP 1996 following trial specific standard operating procedures (SOP) as given in the trial master file, and in accordance with LSHTM Information Management and Security Policy and LSHTM Data Protection Policy. Anonymized data will be stored securely at the LSHTM and separately from any information identifying participants. Paper forms will be stored in numerical order in a secure and accessible place and will be maintained in storage for a period of three years after completion of the study. Electronic data will be stored as csv files and Stata data files (.dta) in LSHTM data centers which provide appropriate levels of environmental and physical security on servers that are managed in accordance with LSHTM Systems Management Policy. Confidential information will be registered with the LSHTM Archivist and Records Manager and data will be stored on a secure server which maintains an audit trail demonstrating system access. At the end of the study, routinely collected HES data for trial participants will be accessed for information on all hospital health service activity during the period between randomization and 12 month postpartum. HES data cover hospital in-patient, outpatients, and accident and emergency attendances.

### Data analysis

#### Outcomes

Statistical analysis will be carried out at the individual level. Every effort will be made to obtain outcome measures for participants, even if some drop out during the course of the group sessions or move out of the local area so have to stop attending gFNP.

Analyses will be carried out using two different types of dataset:

i) The intention-to-treat datasets: data will be analyzed based on participants according to the random allocation irrespective of whether the intervention was or was not entirely or partly taken up.

ii) The per-protocol datasets: as it is possible that participants may not receive the intervention, the intention-to-treat analysis might underestimate the potential efficacy of intervention. A per-protocol analysis will therefore be carried out in addition to the intention-to-treat analysis. The per-protocol datasets will include data pertaining to all outcomes, restricted to those participants who complied fully or partly with their assigned intervention.

The primary analysis will use the intention-to-treat datasets. Demographic and other characteristics at trial entry will be tabulated using the intention-to-treat datasets. No significance tests will be performed to test for differences at baseline. Descriptive statistics for continuous variables will include the mean, standard deviation, median, range and the number of observations. Categorical variables will be presented as numbers and percentages.

The data will be analyzed by multiple regression modeling, with appropriate generalized linear models (GLMs) used to examine the effect of the intervention, fitting baseline measures of outcomes as covariates, where available. A small number of secondary analyses based on explicit hypotheses, for example, subgroup (including ‘looked after’ history)/explanatory analyses (considering compliance with the interventions) will be specified in advance (in a statistical analysis plan). The secondary analyses will include an analysis in which the small groups in which the intervention is delivered will be fitted as a random effect to allow for any potential clustering by group. Sensitivity analyses will be conducted for all primary outcomes. Inverse probability weighting would be considered if missing data were larger than expected and/or there was differential attrition between the trial arms. Additionally, reasons for the differential attrition will be fully explored.

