### Study setting

Sites were included if they responded to an invitation to take part from the FNP National Unit, could demonstrate sufficient women of the relevant age and parity who had given birth in the previous year, and could confirm good links with community midwifery, who also had to sign the expression of interest. Only FNP teams who had delivered the home-based FNP program in its entirety (from birth to child age 24 months) to a cohort of women and with a practising midwife in the team were eligible.

The gFNP program is delivered by two family nurses, one of whom is a practising midwife, in community settings such as Sure Start Children’s Centers, located so that the amount of travelling necessary by group participants is kept to a minimum. Proximity to the location should enhance the rate of attendance and also foster the formulation of social networks. However, so that women from a potentially wider range of home addresses can be recruited to ensure the sample size, funds are available to reimburse intervention participants for travel by public transport to the intervention sessions. Child care is available for any other children. The gFNP program runs from approximately the 16th week of pregnancy to when the babies are 12 months old, meeting weekly or fortnightly during the daytime depending on the stage of the program (14 pregnancy sessions and 30 infancy sessions).

The control group mothers and infants would not be eligible for home-based FNP but will receive all the Universal Core Offer recommended in the Healthy Child Program through midwifery and health visiting services [37]. This is a substantial and universal service for expectant mothers and their infants with a strong evidence base [38] supported by systematic review evidence and NICE guidance. It offers screening tests, immunizations, developmental reviews, information and guidance to support parenting. The latest version has a strong emphasis on pregnancy and the first year of life. Community midwives and health visitors may provide or refer to a range of other community-based or specialist services designed to support young mothers.

Data collection for the study will be conducted by researchers blind to allocation in three visits to participant’s homes (baseline in pregnancy, when infants are two months and twelve months of age), and one telephone contact (when infants are six months old).

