### Randomization

The process will be overseen by the London School of Hygiene and Tropical Medicine Clinical Trials Unit (LSHTM CTU). Identifying information and baseline details of eligible consenting mothers-to-be will be provided by the researchers to the central randomization service at Health Service Research Unit (HSRU), Aberdeen. Minimization criteria will be used to ensure a balance of key prognostic factors using the following two criteria: site and age group (< 20, 20 to 24 years). Allocations to one of two arms will be securely computer generated and delivered by Email to LSHTM. The LSHTM CTU will convey to each gFNP team the names and contact details of women allocated to the intervention arm. The researchers will be blind to allocation.

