#### Process measures

Data forms completed after each group session by the FNs delivering gFNP will provide information on intervention participants’ attendance at each session, the presence of partners and the extent of their understanding and involvement in the content. The ID number used by the FNs for program delivery data will be linked with the trial number.

Qualitative semi-structured interviews will be conducted with selected professionals in each locality to ascertain the extent to which the referral pathways could be strengthened, the likelihood that the service could be successfully embedded in the area and its likely sustainability. These interviews will take place after all recruitment has been completed in each local area with professionals likely, in the future, to be involved in making referrals to the program (in total, at least five community midwives and at least five other relevant health professionals such as general practitioners). At the completion of program delivery in each area, interviews will also be conducted with at least five commissioners of children’s services and with two professionals who are providers of care for ‘looked-after’ young people.

So that the research does not influence the experience of participants in the research, a number of interviews will be conducted after completion of program delivery in each group. At least one family nurse will be interviewed per center and each FNP supervisor will be interviewed about their thoughts on delivering the program and its likely sustainability. They will also be asked about the particular relevance of the gFNP program for women or their partners who have a ‘looked-after’ history or who are currently under the care of social services.

Participants’ views about the acceptability of the program will be assessed using semi-structured face-to-face interviews with a purposive sample (informed by program delivery data) of 20 women who were allocated to receive gFNP support and 5 of their partners.

In-depth semi-structured interviews will be conducted with up to 10 women allocated to receive gFNP (excluding those specified in the previous paragraph) who are or who have a history of being looked after and, if available, their partners, and a similar number of women allocated to standard care to explore their perceptions of the program, or any impacts, and other support needs.

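### The supplementary per-protocol analysis in effect removes only gFNP women who took up none of the program, so it cannot recover undiluted efficacy free of selection bias

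*Protocol article*

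**What the plan says.** All references are to the Protocol article.

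- **Status (Data analysis, Outcomes).** "The primary analysis will use the intention-to-treat datasets". A per-protocol analysis is added because "the intention-to-treat analysis might underestimate the potential efficacy of intervention". It covers every outcome and is "restricted to those participants who complied fully or partly with their assigned intervention". No minimum is given for partial compliance.
- **What is left to the SAP (same section).** Separate "explanatory analyses (considering compliance with the interventions) will be specified in advance (in a statistical analysis plan"). No method is named. The per-protocol analysis itself is not deferred; the article commits to it.
- **Control condition (Study setting).** "The control group mothers and infants would not be eligible for home-based FNP but will receive all the Universal Core Offer". No compliance criterion is attached to this.
- **Access to gFNP (Randomization).** "The LSHTM CTU will convey to each gFNP team the names and contact details of women allocated to the intervention arm". No route by which a control could join a group is described.
- **Attendance (Process measures).** "Data forms completed after each group session by the FNs delivering gFNP will provide information" on the attendance of intervention participants, and this is linked to the trial number.
- **Uptake (Data analysis, Process).** Uptake among women allocated to gFNP is measured by attendance at one or more sessions, set against women who refuse or never come.
- **Baseline measures (Table 1).** AAPI-2 is collected at baseline and 12 months, the CARE Index at 12 months only.

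**The concern.** The purpose given for the per-protocol set is to recover efficacy that non-uptake dilutes. The set chosen cannot do this reliably. Women allocated to gFNP who never take it up can be identified and removed. The control women who would not have taken it up cannot be identified, and they stay in. The arms are then no longer the groups that randomization made comparable.

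If women who attend would have had different outcomes anyway, that difference enters the estimate as if it were an effect of the program. Attending means coming to daytime groups over about 76 weeks, so some link with circumstances that also bear on parenting is plausible, although the document does not measure it.

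What is at stake is interpretation. After an inconclusive intention-to-treat result, a favorable per-protocol estimate could be read as showing that the program works for those who attend, when part or all of it may be selection.

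**Working it through.** **1. The plan's own figure.** Sample size gives a target of 0.5 SD, 90% power, two-sided 0.05 and a pre/post correlation of 0.4. With baseline adjustment, n per arm = 2 × (1.960 + 1.282)² × (1 − 0.4²) / 0.5² = 84.06 × 0.84 = 70.6, rounded up to 71. The stated 71 is reproduced. It supplies the yardstick of 0.5 SD. There is no stated figure for the per-protocol analysis.

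**2. Who is excluded.** The definition is worded for both arms. Controls have nothing to fail to comply with, attendance exists only for gFNP, and partial compliers stay in. So those dropped are, in effect, gFNP women with no uptake. This is an inference from several sections, not a statement in the document.

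**3. Bias formula.** Let c be uptake, g the mean outcome of would-be attenders minus that of non-attenders without the program (in SD, positive meaning better), and τ the effect in attenders.

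- Per-protocol gFNP mean: μₐ + τ
- Control mean: c·μₐ + (1 − c)·μₙ
- Difference: τ + (1 − c)·(μₐ − μₙ) = τ + (1 − c)·g

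The bias is (1 − c)·g.

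**4. Numbers.** Both c and g are assumptions, because the document gives neither.

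| Excluded (1 − c) | g = 0 | g = 0.25 | g = 0.50 | g = 0.75 |
|---|---|---|---|---|
| 10% | 0 | 0.025 | 0.050 | 0.075 |
| 20% | 0 | 0.050 | 0.100 | 0.150 |
| 30% | 0 | 0.075 | 0.150 | 0.225 |

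Against 0.5 SD, the non-zero cells run from 0.025/0.5 = 5% to 0.225/0.5 = 45%. With the stated SD of 10, that is 0.25 to 2.25 AAPI-2 points. A negative g gives the same sizes with the sign reversed.

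**5. Alternative estimator.** If allocation does nothing for women who never attend, intention-to-treat estimates c·τ, and dividing by c returns τ. With τ = 0.5, c = 0.7 and g = 0.5, intention-to-treat gives 0.35, per-protocol 0.5 + 0.15 = 0.65, and CACE 0.5.

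**6. Check by simulation.** The settings were 3,000 trials per scenario, 70 analyzed per arm (100 less 30%), and baseline correlation 0.4. The gap was unrelated to the baseline score, and missingness was unrelated to attendance. The first three rows have no true effect; the last has 0.5 SD in attenders.

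| Uptake, g, τ | Per-protocol estimate (rejection rate) | CACE estimate (rejection rate) |
|---|---|---|
| 85%, 0.5, 0 | 0.08 (7.3%) | 0.01 (4.7%) |
| 70%, 0.25, 0 | 0.08 (8.4%) | 0.01 (4.9%) |
| 70%, 0.5, 0 | 0.15 (13.0%) | 0.00 (5.2%) |
| 70%, 0.5, 0.5 | 0.65 (97.0%) | 0.49 (60.9%) |

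The simulated gap lies wholly outside the baseline score. Any part of it already present in baseline AAPI-2 would be absorbed by adjustment, so for AAPI-2 these figures are the unfavorable case. The CARE Index has no baseline score to adjust for.

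**7. Limits of the alternative.** If compliance were set at more than one session and women below the threshold gained ε, the CACE would be biased by (1 − c)/c × ε. With c = 0.7 and ε = 0.2, that is 0.3/0.7 × 0.2 = 0.09 SD.

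**The case against.** The strongest reply is that nothing decisive rests on this analysis: intention-to-treat is primary, and no power claim or decision rule uses the per-protocol set. That stands, and it limits the weight of the point. A reader might infer that the trial's main conclusion is compromised; the document does not support that.

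A second reply is that compliance analyses are left to an SAP that is not shown. This holds for the explanatory analyses, which may well include a CACE. It does not cover the per-protocol analysis, whose purpose and population the article itself fixes.

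Third, size. A reader might take the 30% dropout in Sample size as the excluded share. That figure is not a never-attender rate; women who start and then stop remain as partial compliers, so the excluded share may be well below 30%. Nor does the document establish the gap or its sign, so a bias in favor of gFNP is plausible but not shown. It would also go too far to say that the plan counts one session of 44 as compliance, since no minimum for partial compliance is set. If the SAP set a higher one, more women would leave and the same formula would apply.

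Finally, CACE is not assumption-free. It removes the bias from dropping non-attenders but needs the exclusion restriction, and a high session threshold weakens it. This also stands and shapes the remedy.

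**Conclusion.** The point holds for a supplementary analysis. As defined, the per-protocol set in effect compares selected gFNP attenders with all controls and cannot be relied on for the purpose the article gives it. For an assumed 10 to 30% excluded and a gap of 0.25 to 0.75 SD, the bias under no effect is about 0.03 to 0.23 SD, or 5 to 45% of the design difference. It vanishes if attenders and non-attenders do not differ and changes sign if attenders would do worse. Three things are assumed: the excluded fraction, the gap, and that exclusions fall on one arm. The last is well supported by the control condition and the one-arm attendance records.

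**What to change.** Keep intention-to-treat primary. For the two primary outcomes, estimate potential efficacy by a CACE with allocation as instrument (for example two-stage least squares) and the same covariates as the primary model. Define compliance mainly as attending at least one session, taken from the linked attendance forms. Use higher session thresholds and per-session estimates only as sensitivity analyses, because the former need a stronger exclusion restriction and the latter also linearity. If the per-protocol analysis is kept, report it as descriptive and not as evidence of efficacy.

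**Cost.** Wording in the protocol and SAP. No new data are needed: attendance is linked to the trial number, uptake is already to be measured, and outcomes are sought from women who stop attending. The confidence interval is wider than for per-protocol (simulated CACE standard error 0.18 SD at 85% uptake and 0.22 SD at 70%). At 70% uptake and 0.5 SD in attenders, power is about that of intention-to-treat (60 to 61% against 57 to 59%). The analysis relies on the exclusion restriction and on an assumption about missing outcomes, which matters with 30% dropout expected and possibly related to attendance. Both should be stated with the result.

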## Methods/Design

### Study design

The study comprises a multi-site randomized controlled trial in which eligible women are allocated (minimized by site and maternal age group) to one of two arms: i) gFNP delivered via 44 sessions delivered over 76 weeks (N = 100); ii) standard care (N = 100). In addition to the quantitative measures used to compare the two groups qualitative methods will be used to provide a better understanding of the results obtained in the trial.

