### Study timeline

The trial commenced in February 2013 and will be completed in January 2016. Recruitment commenced in July 2013 and takes place in seven sites in England (Barnsley, Dewsbury, Lewisham, Nottingham, Sandwell, South Tyne and Wear and Waltham Forest) through until January 2014. Figure 1 provides details of the timeline for each participant, which will extend from the time that they book in with their midwife (on average at 8 to 12 weeks gestation) through to the end of the study, when their infants are at least 12 months old. The specific time will vary depending on their gestation at booking but will range from 82 to 86 weeks. The intervention arm will receive the gFNP program for 76 weeks on average (from 16 weeks gestation to infant 12 months).

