### Sample size

The sample size was calculated for the two primary outcomes, the revised Adult Adolescent Parenting Inventory (AAPI-2) [39] and the observational CARE Index [40-42]. The standard deviation (SD) of the AAPI-2 is 10, with differences of 6.7 identified in the normative sample between abusive and non-abusive adult females [39]. The standard deviation for the CARE Index is expected to be around 2.3 [41].

For this individually randomized trial, we propose to recruit sufficient mothers and babies (families) to allow the trial to detect a difference between groups of 0.5 standard deviations, with 90% power at a significance level of 0.05 (2-tailed); this is considered to represent a moderate size of effect [43]. Basing calculation on the AAPI-2, very conservatively assuming a correlation of 0.4 between pre and post intervention scores we would need at least 71 families in each arm of the trial to detect this difference. Allowing for an expected 30% drop out rate (based on the first two applications of the program in England) we would need to recruit a minimum of 84 families per arm of the trial. We therefore propose, conservatively, to recruit a minimum of 100 families per arm (N = 200). In the intervention arm this will consist of 10 groups of (generally) 10 families (N = 100), with 2 groups provided per site. However, given that the minimum number required for a viable group is 8, 7 sites are involved in the trial so that it will be possible to recruit a minimum of 208 (if one site proves able to deliver only one group of 8) and potentially at least 224 participants (2 groups of 8 per site plus the same number of controls). It was necessary to have two more sites than the five originally proposed to cope with the possibility that in one or more areas area the minimum number of women would not be recruited to form a viable group. The proposed sample size would similarly allow us to detect a change of approximately 0.5 standard deviations in the CARE index [40-42]. We would therefore expect to be able to detect a difference at follow-up between arms of the trial of approximately 1.2 with 90% power and a 5% level of significance.

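### The outcome model does not name site and age group, the factors used to minimize allocation, so to the extent they are prognostic its standard errors would be conservative, most visibly for CARE

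*Protocol article*

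**What the plan says.** The Randomization section of the protocol article gives the allocation method and its reason: "Minimization criteria will be used to ensure a balance of key prognostic factors using the following two criteria: site and age group". The Study design section repeats it: "eligible women are allocated (minimized by site and maternal age group) to one of two arms". Age group has two levels, under 20 and 20 to 24 years. The Study timeline section says that recruitment "takes place in seven sites in England".

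The Outcomes subsection of Data analysis describes the model: "The data will be analyzed by multiple regression modeling, with appropriate generalized linear models (GLMs) used to examine the effect of the intervention". The same sentence continues with the only covariates it names: "fitting baseline measures of outcomes as covariates, where available". Site and age group are neither named nor excluded. The subsection does mention a statistical analysis plan, but as the place for a small number of secondary analyses (subgroup and explanatory), not for the covariates of the main model.

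Table 1 in Data management lists the AAPI-2 at baseline and at 12 months, and CARE at 12 months only. The text there agrees: "At 12 months postpartum, data collection will also include independent video-recorded observations of the mother and infant". PSI and PSOC are first measured at two months and also have no baseline value.

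**The concern.** Minimization makes the arms more alike on site and age group than chance would. Any outcome variance due to these factors then largely cancels out of the treatment comparison. A model that leaves the factors out still counts that variance as residual error, so its standard error is larger than the true one. Confidence intervals come out too wide and p-values too large.

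The design treats the two factors as important enough to constrain allocation, yet the sentence that states the model does not carry them through. CARE is the clearest case: with no baseline value, the stated rule gives that primary outcome no covariate.

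An association with parenting outcomes is plausible. Under the eligibility criteria every woman under 20 has had a previous live birth and no woman aged 20 to 24 has, so age group is also parity. How strong the association would be, the documents do not say.

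**Working it through.** **Inputs from the protocol article.** Sample size section: target difference 0.5 SD, 90% power, two-sided 5% level, pre/post correlation 0.4 for the AAPI-2, 71 evaluable per arm, 100 recruited per arm, 30% dropout. Evaluable per arm: 100 × 0.7 = 70. Seven sites, two age groups.

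**Assumed input.** R², the share of outcome variance explained by site and age group, is not given. The range used is 0 to 0.20. For the AAPI-2 it means the share of the variance left after baseline adjustment.

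**Step 1: reproduce the plan's figure.** With baseline adjustment, n = 2(1.96 + 1.2816)² × (1 − 0.4²)/0.5² = 70.6, so 71 per arm, as stated. This calculation assumes nothing about site or age group.

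**Step 2: the two standard errors.** Let s be the SD in SD units: 1 for CARE, √(1 − 0.16) = 0.917 for the AAPI-2. With the factors exactly balanced between arms:

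- true SE = s√(1 − R²)√(2/n)
- SE reported without the factors = s√(2/n)
- ratio = 1/√(1 − R²)
- actual two-sided alpha without the factors = 2[1 − Φ(1.96 × ratio)]
- power without the factors = Φ(0.5/true SE − 1.96 × ratio)
- power with the factors = Φ(0.5/true SE − 1.96)

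**Step 3: results at 70 evaluable per arm.**

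| R² | SE ratio | Actual alpha | CARE power, without → with | AAPI-2 power, without → with |
|---|---|---|---|---|
| 0 | 1.000 | 0.050 | 84.1% → 84.1% | 89.8% → 89.8% |
| 0.02 | 1.010 | 0.048 | 84.3% → 84.8% | 90.0% → 90.3% |
| 0.05 | 1.026 | 0.044 | 84.7% → 85.9% | 90.3% → 91.2% |
| 0.10 | 1.054 | 0.039 | 85.4% → 87.7% | 90.9% → 92.5% |
| 0.20 | 1.118 | 0.028 | 86.8% → 91.1% | 92.2% → 95.0% |

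Worked example, CARE at R² = 0.10: √(2/70) = 0.1690; true SE = 0.9487 × 0.1690 = 0.1604; 0.5/0.1604 = 3.118. Without the factors: Φ(3.118 − 2.066) = 85.4%. With them: Φ(3.118 − 1.960) = 87.7%. The gap is 2.3 points.

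**Step 4: simulation.** 3000 runs per case were made with seven sites, two age groups, biased-coin minimization, 200 randomized, 30% lost at random, and a linear model with and without site and age group. CARE power went from 83.4% to 82.4% at R² = 0, from 83.1% to 83.9% at 0.05, from 84.0% to 86.7% at 0.10, and from 84.4% to 89.7% at 0.20. The simulation error of each power figure is about √(0.84 × 0.16/3000) = 0.7 points, so the drop at R² = 0 is within error.

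The simulation shows less conservatism than Step 3, because minimization followed by random loss does not leave exact balance. At R² = 0.20 under no effect, the mean reported SE without the factors was 0.169 and the estimate's actual SD was 0.157, a ratio of 0.169/0.157 = 1.08. The rejection rate was 0.042. The SE ratios and alphas in Step 3 are therefore the limit under exact balance. The power gap was 5.3 points in simulation at R² = 0.20, against 4.3 by formula.

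**The case against.** The strongest reply is that this is a condensed article whose analysis plan is not shown, and that the text is silent on site and age group. A reader might infer that the model adjusts for baseline outcomes and nothing else. The article does not say so, and an unseen plan may add the factors. That part of the reply stands. It does not remove the point, because the article itself states a covariate set for the main model and its pointer to an analysis plan is attached to the secondary analyses. As written, the stated set does not match the allocation method.

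Second, describing the factors as prognostic is a label, not a magnitude. At R² = 0 nothing is lost, and at 0.02 the CARE gap is half a point. This stands, and the size must be given as conditional.

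Third, a reader might infer that the omission biases the treatment effect or explains why CARE falls short of its stated 90% power. Neither follows. A linear model remains unbiased. In Step 3, CARE power without the factors rises with R², from 84.1% at 0 to 86.8% at 0.20. The gap between 84.1% and 90% exists already at R² = 0; it comes from having no baseline CARE value and from the dropout allowance, which are separate matters.

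Fourth, 1/(1 − R²) = 1.11 at R² = 0.10 might be read as the power of 11% more families. It describes the width of the reported interval. Minimization has already delivered part of the precision, so the gap is 85.4% to 87.7%, not 84.1% to 87.7%.

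**Conclusion.** The point holds as a mismatch between allocation and the stated model, with a modest and conditional cost. For R² from 0 to 0.20, standard errors would be too large by 0% to about 12% and actual alpha would run from 0.050 to 0.028, both under exact balance. CARE would forgo 0 to about 4 points of power against an adjusted analysis at 70 evaluable per arm, and about 2 points at R² = 0.10. The AAPI-2, which has a baseline value, would forgo 0 to about 3 points.

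These figures rest on the assumed R² range, a normal approximation, 30% loss unrelated to outcome, and a linear model for both primary scores. The error is on the safe side: it makes a real effect harder to show and does not raise the false-positive rate.

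A reader might also conclude that every model needs a random effect for the gFNP group, or that CARE, PSI and PSOC must be adjusted for baseline AAPI-2 and EPDS. Minimization by site and age group requires neither. The article places the group random effect among its secondary analyses, and clustering is a separate question.

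**What to change.** In the Outcomes subsection of Data analysis, state that the models for both primary outcomes, and for the secondary outcomes, include site and age group as covariates, plus the baseline value of the outcome where one is measured. Nothing else in the subsection needs to change for this point.

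The cost is one sentence and seven degrees of freedom (six for seven sites, one for two age groups) out of about 140 evaluable families (2 × 70). Both factors are already recorded for minimization, so no new data are needed. If the factors turn out not to be prognostic, the simulation at R² = 0 puts the price of adjusting at about one point of power, which is within simulation error.
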